### Statistical methods

3.12

This protocol is primarily based on comparing the baseline information of the participants with their information on Weeks 4 & 8 of their intervention. With regards to this, we will use Repeated Measures ANOVA for comparing the effect of time on the participants' changes in chronic headache characteristics, psychiatric symptoms, and medicine intake. Additionally, we will compare the interaction effect of time* groups to discover which of the three groups would show most significant changes across time as measured independently for each of the study's scales.

For each of the task-based groups, we will explore the total missed days and attrition at each of the task groups to discover the level of adherence for the two task-based groups. The diaries will also be compared across time to discover how participants manage their headaches via different alternatives and whether there is a change in their trend of headache medicine intake.

Finally, the EEG data analysis will be applied for within-subject and between subject comparisons to determine whether there is a change in adults with chronic migraine's peak alpha frequency over time and during their headache experiences as a function of their practices.

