## Hypotheses

2

The main goal of the presented RCT protocol is to evaluate how 8 weeks of neurofeedback mindfulness using a wearable EEG headband could moderate headache experience (including frequency and intensity), headache management self-efficacy, psychiatric symptoms (i.e., anxiety and depression) and dependence on analgesics for adults with chronic migraine who are also identified as naïve meditators. The specific measures are described in more detail below. The following hypotheses are tested in this RCT.1.After completing the intervention, neurofeedback mindfulness will improve headache experience across time via:a.Decreased migraine disabilityb.Decreased migraine intensityc.Increased headache management self-efficacya.Decreased anxietyb.Decreased depressionc.Decreased level of dependence on medication.2.Participants in the neurofeedback mindfulness group will have significantly lower scores in migraine disability and intensity, and significantly higher scores in headache management self-efficacy when compared to the attention control group and the waitlisted group.3.Participants in the neurofeedback mindfulness group will have lower anxiety and lower depression scores when compared to the attention control group and the waitlisted group.4.Neurofeedback mindfulness participants will have a significant decrease in the level of dependence on medication, compared to those in the controlled intervention and waitlisted groups.5.There will be no impact of participants' belief in meditation on any of the measured criteria (e.g., migraine characteristics and psychiatric symptoms) across time.

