### The assigned tasks

3.6

In this study, the participants will be randomly allocated in three groups of neurofeedback-mindfulness, the controlled intervention, and waitlisted groups. The allocation will be done using stratified randomization to ensure equal distribution (1:1:1) among groups.1.The neurofeedback mindfulness groupThis group is asked to sit comfortably in a quiet area and do one of ten beginner self-guided mindfulness sessions on mind-body scanning techniques from within the MUSE app. Each session includes a brief explanation for 2–3 min before the practice. The participants repeat the same sessions throughout the intervention.1.Introduction to mindfulness: a brief review of mindfulness as a nonjudgmental observation of body and mind.2.Training a puppy: how to monitor emotions and control reactions to different states of mind.3.Sensation of breath: the importance of mindful breathing techniques.4.Counting breaths: how to inhale and exhale properly.5.Sitting comfortably: how to modify positions for mindfulness practices.6.Finding your soundscapes: monitoring the states of mind and how they are associated with the given neurofeedback sounds.7.Dealing with distraction: describing nonreactivity and acceptance of different states of mind.8.Working with discomfort: how to mindfully adjust the states of mind in unfavourable conditions.9.Lowering the bar: Moderating expectations from practices and accept the present state of mind without changing it.10.Bridging to daily life: bringing attention to how the state of acceptance could be conceptualized in everyday routines.

Once the participants start their practices, they receive sounds for their real-time brain activities: thunderstorm for an active state, ocean waves for a neutral state, and birds chirping for a relaxed state. For each 5 s of consistent relaxed state, the participants are reinforced with points.2.The attention control group

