### Participants

3.9

According to A priori G*power software calculation for this study considering both between-subject and within-subject effects, a sample size of 66 is expected to detect significance level of 0.05 with 95 % power through our planned statistical analysis test, i.e., Repeated Measures ANOVA. We aim to look at the effect of time by comparing the baseline with mid-/post intervention reports of the participants for each of the six measurements independently; moreover, we will compare the interaction of time*groups separately for each of our six scales. We will initially allocate 180 participants; yet with reference to the previous studies [22], we could expect up to 50 % of attrition. After applying inclusion and exclusion criteria, participants will be selected for either the meditation, the control, or the waitlisted group. We speculate a higher number of attritions in the meditation and control groups regarding the complexity of the given tasks as compared to the waitlisted group. Fig. 3 provides a flowchart for the number of expected participants at each stage of the study.

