### The instruments

3.11

In this study, six measurements are given to participants at three time points during the study: before the intervention (Week 1), during the intervention (Week 4) and after completing the intervention (Week 8). On average, the total amount of time to complete six questionnaires is estimated around 13 min. These measurements (described in detail below) collect information about migraine disability (MIDAS), headache intensity (HIT-6), headache management self-efficacy (HMSE), anxiety (BAI), depression (CES-D), and severity of dependence on medications (SDS).1Migraine Disability Assessment Scale (MIDAS)

This 5-item instrument focuses on the number of headache-impacted missing days in the migraine population. MIDAS is shown to have significantly high internal consistency scores in United States (Cronbach's α = 0.76) and the UK (Cronbach's α = 0.73) [39].2Headache Impact Test-short form (HIT-6)

This 6-item scale collects information about the intensity of the headache attacks with high reliability of 0.90 Cronbach's ***α*** ([40]). This measurement is a short and sound psychometrical tool to assess how participants evaluate their headache severity.3.Headache Management Self-Efficacy Scale (HMSE)

This measurement is a 25-item scale that measures individuals' perceived level of coping and headache-related disability management with an excellent internal consistency (Cronbach's α = 0.90) [41]. The HMSE score predicts headache-related disability, as shown in MIDAS, regardless of the headache intensity, as usually shown in HIT-6 [41].4BECK Anxiety Inventory (BAI)

This 21-item instrument is a self-report of physical and cognitive symptoms of anxiety on and is validated with a moderate correlation with the revised Hamilton Anxiety Rating Scale (*r* = 0.51)([42]). Internal consistency of this measure is significantly high (Cronbach's α = 0.92) and test-retest reliability in a 1-week period was also acceptable (Cronbach's α = 0.75) [42].5.The Center for Epidemiologic Studies Depression (CES-D)

This validated 20-item scale is a short self-report of the original version with 300 items [43]. The internal consistency of this instrument is high (Cronbach's α = 0.85–0.90) and test re-test reliability is also acceptable (0.45–0.70) [39].6.Severity of Dependence Scale (SDS)

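### Testing Hypotheses 2-4 by time*group with Week 1 as a response level is valid under randomisation, but less precise than adjusting for the Week 1 score already collected

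*Protocol article*

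**What the plan says.** Section 3.12 (Statistical methods) sets the frame: "This protocol is primarily based on comparing the baseline information of the participants with their information on Weeks 4" and 8. It continues, "we will use Repeated Measures ANOVA for comparing the effect of time on the participants", and for the arms, "we will compare the interaction effect of time* groups to discover which of the three groups would show most significant changes across time", separately for each scale. Section 3.9 (Participants) repeats the approach, "We aim to look at the effect of time by comparing the baseline with mid-/post intervention reports of the participants", and bases the sample size on the same test: "a sample size of 66 is expected to detect significance level of 0.05 with 95 % power".

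Section 3.11 (The instruments) makes Week 1 one of the measurement times for every scale: "six measurements are given to participants at three time points during the study: before the intervention (Week 1", followed by Weeks 4 and 8. No section uses the Week 1 score as a covariate.

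The hypotheses that need a comparison of arms are 2 to 4. Hypothesis 2 begins "Participants in the neurofeedback mindfulness group will have significantly lower scores in migraine disability and intensity" and sets that arm against both the attention control and the waitlist.

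**The concern.** When Week 1 is a level of the time factor, time*group compares the arms on their unadjusted changes from Week 1. Randomisation makes the arms equal in expectation before treatment, so subtracting the whole Week 1 score removes more than its correlation with follow-up justifies and adds noise. Regressing on the Week 1 score removes only the part that predicts follow-up.

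The protocol states this choice twice and sizes the trial on it, so it is not a detail left to a later document.

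What is at stake is mainly the comparison with the attention control. The Introduction gives that comparison the job of showing whether mindfulness is needed or whether simple attention would do. If a real difference is missed through avoidable imprecision, the result could be misread as showing that attention is enough.

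**Working it through.** **The plan's own figure.** Section 3.9 gives N = 66, alpha 0.05 and 95% power, but no effect size f or correlation, so 66 cannot be strictly reproduced. Using λ = f²·N·m·ε/(1−ρ) for the interaction, with f = 0.25 and ρ = 0.5 assumed:
- 3 groups, 3 measurements: N = 54.
- 3 groups, 2 measurements: N = 66.
- 3 groups, 3 measurements, ε = 0.75: N = 66.

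So 66 fits some ordinary inputs for the planned test.

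**Inputs**
- From section 3.9: 180 allocated and up to 50% attrition, so 180 × 0.5 = 90 completers. With the 1:1:1 allocation of section 3.6 that is 30 per arm.
- Assumed: equal variances, equal correlation ρ between visits, a 0.5 SD difference (for the follow-up mean, at both visits), two-sided alpha 0.05.
- Guide to ρ: section 3.11 quotes test-retest values of 0.45-0.70 (CES-D) and 0.75 over one week (BAI). These are only proxies for a baseline to follow-up correlation.

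**Variance per participant, in SD² units**
- Week 8: change 2(1−ρ); adjusted 1−ρ². Ratio (1+ρ)/2.
- Mean of Weeks 4 and 8: change 3(1−ρ)/2; adjusted (1+ρ)/2 − ρ². Ratio (1+2ρ)/3.

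Both ratios are below 1 for every ρ below 1. At ρ = 0.45 they are 0.725 and 0.633; at ρ = 0.75 they are 0.875 and 0.833. Over that range the planned contrast therefore carries 14-38% more variance at Week 8 (1/0.875 to 1/0.725) and 20-58% more for the follow-up mean (1/0.833 to 1/0.633).

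**Pairwise power at 30 per arm.** Noncentral t with noncentrality 0.5/√(2V/30); df 87 for change and 86 for adjusted.

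| ρ | Week 8: V, change → adjusted | Week 8: power | Mean of 4 and 8: V, change → adjusted | Mean: power |
|---|---|---|---|---|
| 0.3 | 1.40 → 0.91 | 36.7% → 51.9% | 1.05 → 0.56 | 46.4% → 72.5% |
| 0.5 | 1.00 → 0.75 | 48.2% → 59.9% | 0.75 → 0.50 | 59.9% → 77.3% |
| 0.7 | 0.60 → 0.51 | 69.6% → 76.5% | 0.45 → 0.36 | 81.5% → 89.1% |
| 0.8 | 0.40 → 0.36 | 85.7% → 89.1% | 0.30 → 0.26 | 93.8% → 96.4% |

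A simulation of 4,000 trials at ρ = 0.5 also gave 48% and 60% for the Week 8 pair.

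**The plan's own omnibus test.** Let one arm shift by 0.5 SD at both follow-up visits, with ρ = 0.5 and 30 per arm. The squared group deviations sum to 4/9 + 1/9 + 1/9 = 2/3.
- Planned time*group: squared interaction effects sum to 2/3 × (0.5² × 2/3) = 0.111, so λ = 30 × 0.111/0.5 = 6.67 on 4 df and power is about 51%.
- Same 4-df test with Week 1 adjustment: λ = 30 × 2/3 × 0.5 = 10 and power is about 70%.

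At 22 per arm (N = 66) the same pair is 37% and 54%. So the loss is not created by choosing a pairwise contrast.

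**The case against.** **The contrast is not the one the plan names.** The protocol specifies time*group, not a Week 8 pairwise difference. Where effects are equal at Weeks 4 and 8, an ordinary repeated-measures contrast of the follow-up mean against Week 1 equals the Week 8 ANCOVA at ρ = 0.5 (both 60%) and beats it at ρ = 0.7. This is correct, and it means the choice of contrast matters as much as the adjustment. But it compares different contrasts. Like for like, the adjusted version is more precise at every ρ below 1, including for the 4-df test.

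**The inefficiency is already priced into 66.** This stands. A reader might infer that 66 is too small, but the documents do not support that: 66 was calculated for this same test, and 66/(1−0.5) = 132 is below the 180 to be allocated. At ρ = 0.5, an effect giving time*group 95% power at 66 (f = 0.221) gives about 99% at 90.

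**Week 1 is not a clean pre-allocation score.** This also stands. Allocation and the task description (3.3) precede the questionnaire completed on the day of the initial meeting (3.4). Waitlist participants are told their arm (3.6), and nobody is blinded (3.8). Only SDS is named in the questionnaire sent before allocation (3.2). A covariate recorded before the arm is known therefore cannot be required for the other five scales without new data. Section 3.9 also expects more attrition in the two task arms, so completers need not be equal at Week 1, and change and adjusted contrasts could then differ in target as well as in precision. Both issues touch the planned ANOVA as well.

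**Strata.** Section 3.6 says "The allocation will be done using stratified randomization to ensure equal distribution (1:1:1) among groups" but names no factors. A reader might call their absence from the model an error. Model detail of this kind is commonly left to a fuller document, and no loss can be calculated, so the point is secondary.

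**Conclusion.** The point holds as one of efficiency. A reader might infer that the planned test is biased or has the wrong type I error. It does not: under randomisation time*group is valid, and the protocol misstates nothing here. What it does is choose a less precise between-arm comparison than its own data allow.

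The loss is worth recovering at moderate correlations: at ρ = 0.5, about 12 points of pairwise power at Week 8 and 17 for the follow-up mean; at ρ = 0.7, about 7 and 8. It is about 3 points at ρ = 0.8, and little where power is already near its ceiling. These sizes rest on the assumed 0.5 SD, equal correlation between visits, 30 completers per arm, and Week 1 scores that are equal in expectation across arms. The protocol gives neither the effect size nor ρ.

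**What to change.** In sections 3.9 and 3.12, for Hypotheses 2-4 and for each scale:
- Model Weeks 4 and 8 as outcomes, with group, visit, group*visit, the Week 1 score of the same scale, and its interaction with visit.
- Report adjusted differences, mindfulness versus attention control and mindfulness versus waitlist, with 95% confidence intervals. State in advance whether these are taken at Week 8 or averaged over Weeks 4 and 8.
- Use the Week 1 score as collected. Note as a limitation, shared with the present model, that it is self-reported after the arm is known. For SDS, the initial questionnaire of section 3.2 can supply a covariate from before allocation.
- Add the randomisation strata as fixed terms if wanted; this is secondary.
- Keep the Repeated Measures ANOVA for change over time under Hypothesis 1. Either re-express the G*Power statement for the new model or label it as referring to the Repeated Measures ANOVA.

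Used this way, the change needs no new data, visits or participants. It costs a few degrees of freedom, an assumed linear relation to the Week 1 score, and the revised power statement.

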## Discussion

4

This RCT protocol has a pioneering concept of introducing a new self-guided neurofeedback mindfulness meditation in adults with chronic migraine compared to a novel controlled intervention and a waitlisted group. Our study protocol includes details on the most important challenges, specifically data collection and issues with confidentiality while using a third-party app. Most importantly, we need to evaluate how to keep participants in a consistent and thorough routine. To motivate participants, we have recommended manual text reminders which support participants with easy access to troubleshooting. Since chronic migraine a lifelong, it is important to take measures for both respecting their choice of withdrawal, as well as reinforcing participants' adherence throughout the study. The recommended protocol is designed to keep a consistent practice balance for adults with chronic migraine to collect information about the effectiveness of neurofeedback mindfulness meditation. We also introduce portable EEG headband as a means of collecting daily information from the participants’ practices.

## Ethics approval

This study is approved by the Behavioural Research Ethics Board at the University of Saskatchewan (Beh-REB 1986). The researchers are all trained by the Tri-Council Policy Statement: Ethical Conduct for Research Involving Humans (TCPS 2).

## Data Availability

No data was used for the research described in the article.
